# Magnetic resonance imaging for cerebral lesions during minimal invasive mitral valve surgery: study protocol for a randomized controlled trial

**DOI:** 10.1186/s13063-017-1821-y

**Published:** 2017-02-21

**Keywords:** Minimal invasive surgery, Mitral valve, Stroke, Magnetic resonance

## Abstract

**Background:**

Recent data have highlighted a higher rate of neurological injuries in minimal invasive mitral valve surgery (MIMVS) compared with the standard sternotomy approach; therefore, the role of specific clamping techniques and perfusion strategies on the occurrence of this complication is a matter of discussion in the medical literature.

The purpose of this trial is to prospectively evaluate major, minor and silent neurological events in patients undergoing right mini-thoracotomy mitral valve surgery using retrograde perfusion and an endoaortic clamp or a transthoracic clamp.

**Methods/design:**

A prospective, blinded, randomized controlled study on the rate of neurological embolizations during MIMVS started at the University of Turin in June 2014. Major, minor and silent neurological events are being investigated through standard neurological evaluation and magnetic resonance imaging assessment. The magnetic resonance imaging protocol includes conventional sequences for the morphological and quantitative assessment and nonconventional sequences for the white matter microstructural evaluation. Imaging studies are performed before surgery as baseline assessment and on the third postoperative day and, in patients who develop postoperative ischemic lesions, after 6 months.

**Discussion:**

Despite recent concerns raised about the endoaortic setting with retrograde perfusion, we expect to show equivalence in terms of neurological events of this technique compared with the transthoracic clamp in a selected cohort of patients. With the first results expected in December 2016 the findings would be of help in confirming the efficacy and safety of MIMVS.

**Trial registration:**

ClinicalTrials.gov, Identifier: NCT02818166. Registered on 8 February 2016 – trial retrospectively registered.

**Electronic supplementary material:**

The online version of this article (doi:10.1186/s13063-017-1821-y) contains supplementary material, which is available to authorized users.

## Background

Since first being reported in the medical literature regarding minimal invasive mitral valve surgery (MIMVS) in the late 1990s, several techniques have been described with different modes of arterial perfusion and aortic clamping [1, 2]. Among these, retrograde arterial perfusion (RAP) with an endoaortic clamp (EndoClamp/Intraclude, Edwards Lifesciences, Irvine, CA, USA) (EAC) and RAP with a transthoracic clamp (TTC) are the most frequently reported.

Despite excellent outcomes having been achieved in terms of feasibility and effectiveness, MIMVS adoption is still limited; a report from the STS database by Gammie et al. indicates that the right mini-thoracotomy approach is performed in only 20% of the overall isolated mitral valve (MV) procedures [3]. Several reasons may account for this limited adoption: the transition from a median sternotomy to a right mini-thoracotomy approach requires, even for established surgeons, additional training with a challenging learning curve; the learning curve is also demanding for other members of the team such as anesthesiologists, perfusionists and scrub nurses; and investments in video-assistance platforms, different surgical instruments and perfusion cannulae are required [2]. Moreover, there is still debate in the medical literature regarding the rate of vascular and neurological events in the minimal access approach and regarding the role of different arterial perfusion and aortic clamping techniques.

Recent studies have focused on RAP as the main risk factor for neurological complications in MIMVS [4–6]; however, this only seems to be confirmed in cases of severe peripheral vascular disease [7, 8].

To date, in the medical literature, all the reports regarding neurological complications after MIMVS are retrospective analyses and most of them only take into consideration major neurological outcomes. However, it is known that neurological injury may also occur as minor neurological dysfunctions or silent neurological events [9, 10]. Therefore, prospective randomized studies comparing different modes of aortic clamping techniques, using more sensitive and precise diagnostic tools, should be considered to highlight even the subclinical neurological injuries after MIMVS and to identify the safest approach to adopt.

The aim of this report is to describe the design of a randomized controlled trial regarding the safety, in terms of neurological outcome, of two different modes of aortic clamping in MIMVS through the use of magnetic resonance (MR) imaging.

## Methods/design

### Study design and objectives

A prospective, blinded, randomized controlled study of the rate of neurological embolizations during MIMVS started at the University of Turin – Cardiothoracic Department and Neuroradiology Department – in June 2014 (ClinicalTrials.gov, ID: NCT02818166 – trial retrospectively registered). The study protocol was reviewed and approved by the Institutional Ethics Committee (protocol 0063123). The purpose of this study is to prospectively evaluate major, minor and silent neurological events in patients undergoing MIMVS with RAP and an EAC or a TTC. The primary endpoint is to assess the difference in terms of MR imaging events between the EAC and the TTC. The secondary endpoints are to determine the incidence of new neurological lesions on postoperative MR imaging in patients undergoing MIMVS and to assess the evolution of the new cerebral lesions at the MR imaging follow-up (6–12 months later). To detect major and minor neurological complications, all patients undergo standard neurological examination performed by intensivists and/or cardiac surgeons evaluating sensory, motor, locomotion, cranial nerve, language and reflex deficits after awakening from anesthesia and on every subsequent day of their hospital stay. Silent neurological lesions are evaluated through MR imaging assessment; imaging evaluation is performed by blinded radiologists with a 3 T system (Philips INGENIA 3 T). The protocol includes conventional sequences for the morphological and quantitative assessment (3D-FLAIR, 3D-T1-TSE, DWI, T2-FFE) and nonconventional sequences for white matter microstructural evaluation (Diffusion Tensor Imaging – DTI with fractional anisotropy and mean diffusivity). No contrast enhanced is used.

Inclusion criteria reflect the current indications for MV surgery [11]. Details of major inclusion and exclusion criteria are reported in Table 1.

**Table 1 Tab1:** Major inclusion and exclusion criteria

Major inclusion criteria	
Indications for MV surgery for significant mitral regurgitation	
Patient selected for elective MIMVS	
Age >18 years and <80 years	
Provision of written informed consent	
Major exclusion criteria	
Age <18 years and >80 years	
Peripheral vascular disease	
Permanent or paroxysmal atrial fibrillation	
Atrial septal defects	
Previous cardiac surgery	
Dilatation of the ascending aorta	
Contraindications to MR imaging (e.g., permanent pacemaker in situ, tatoo, claustrophobia, etc.)	
Neurocognitive impairment	
Previous stroke or transient ischemic attack	
Autoimmune diseases	
Neoplastic diseases	
Cerebral inflammatory diseases	
Chronic headache	
Celiac disease	
Drug and alcohol abuse	

*MIMVS* minimal invasive mitral valve surgery

All patients are screened for initial study eligibility by the principal investigator. Both transthoracic echocardiographic studies and aorto-iliac-femoral vessel angiography or computed tomography (CT) scan are evaluated to determine patient eligibility.

Before surgery, an initial MR imaging study is performed as a baseline assessment. If no contraindications arise in the postoperative period (e.g., definitive pacemaker implantation), a second MR imaging is performed on the third postoperative day. In patients who develop postoperative ischemic lesions, a follow-up MR imaging is performed after 6 months (see Fig. 1, and Fig. 2 and Additional file 1 for the SPIRIT figure and populated SPIRIT Checklist, respectively). The right mini-thoracotomy protocol for MV surgery used in our department has been previously described [12–14].

**Fig. 1 Fig1:**
[figure not shown]
Study design

**Fig. 2 Fig2:**
[figure not shown]
Standard Protocol Items: Recommendations for Interventional Trials (SPIRIT) figure

### Statistical considerations

Data regarding patients’ details, type of surgical procedure and outcomes are entered prospectively into a dedicated database by one of the investigators. Missing or aberrant data will be verified. The rate of neurological events over time will be studied by the classical technique of the time series: this rate will be thus estimated at three sequential time points by MR imaging scan (at baseline, 3 days after surgery and 6 months after surgery). *P* values will be obtained by the two-sided exact method, at the conventional 5% significance level. Data will be analyzed using R 3.3.1 (R Foundation for Statistical Computing, Vienna, Austria: http://www.r-project.org/).

The association between the occurrence of neurological events and the categorical variables will be analyzed by the Fisher’s exact test, describing the outcome as relative frequencies. The relationship between the occurrence of neurological events and the continuous variables will be estimated using the Mann-Whitney test; these results will be expressed as the median (interquartile range (IQR)). The odds ratio of the occurrence of neurological events (categorical dependent variable: major, minor and silent) will be investigated by a complete series of univariate/multivariate binary logistic regression models, performed for the abovementioned covariates (categorical and continuous independent variables).

According to the medical literature, the incidence of MR imaging events in patients undergoing MV surgery through the standard sternotomy approach has been reported to range from 29% to 45% [15, 16]. Assuming the lower value (only MV procedures and patients without vascular disease enrolled in the present study) a total of 706 patients (353 patients per group) would have an 80% chance of demonstrating equivalence between the EAC and theTTC, with a margin of 10% and a 95% confidence. With an expected loss to MR imaging control of 5% (definitive pacemaker implantation, etc.) the total required sample size is estimated to be 741.

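### The MR event rate planned at baseline, day 3 and 6 months cannot be estimated for the cohort, because only patients with a postoperative lesion are scanned at 6 months

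*Protocol article*

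**What the plan says.** The Statistical considerations section of the protocol article opens its outcome analyses with this sentence: "The rate of neurological events over time will be studied by the classical technique of the time series". It then adds that "this rate will be thus estimated at three sequential time points by MR imaging scan", and lists the points as baseline, day 3 and 6 months after the operation. No restriction on the population is given.

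The Study design and objectives section sets out who is scanned and when:

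- **Baseline:** "Before surgery, an initial MR imaging study is performed as a baseline assessment". No patients are excepted.
- **Day 3:** "a second MR imaging is performed on the third postoperative day", unless a contraindication such as a pacemaker has arisen.
- **Follow-up:** "In patients who develop postoperative ischemic lesions, a follow-up MR imaging is performed after 6 months". The Abstract has the same restriction: "in patients who develop postoperative ischemic lesions, after 6 months".

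One secondary endpoint in Study design and objectives uses the follow-up scan. It is "to assess the evolution of the new cerebral lesions at the MR imaging follow-up (6–12 months later"). The time there is 6–12 months. The Abstract, the later text of the same section and Statistical considerations all say 6 months.

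**The concern.** The first two scans cover essentially the whole cohort. The third covers only patients in whom a lesion has already been found. A rate needs a denominator, and at 6 months neither available choice gives the cohort rate:

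- Dividing by those scanned conditions on being a case. In that group the day-3 rate is 100% by construction, so the later rate can only stay level or fall.
- Dividing by all patients assumes that nobody unscanned has a late lesion. The schedule collects nothing that could check this.

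The first point differs in kind as well. A scan before surgery shows lesions already present, not events of surgery. Excluding patients with previous stroke or transient ischemic attack does not rule out silent lesions. The three points would thus count pre-existing findings, new findings, and persistence of findings in cases.

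At stake is a secondary result. A series reported as planned could be read as the course of cerebral injury in the trial population. Its level at 6 months would in fact depend on an unstated denominator, possibly chosen after the data are seen.

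**Working it through.** **Inputs from Statistical considerations.** Assumed MR event rate 29% (literature range 29% to 45%), equivalence margin 10%, 80% power, 706 patients (353 per group), and 741 after a 5% allowance for loss to MR control. The 706 is the number before that allowance, so it serves as the number with a usable day-3 scan.

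**Input not in the document.** The share of day-3 lesions still visible at follow-up. It is assumed here and ranged from 25% to 100%.

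**Step 1: reproduce the plan's figure.** Two one-sided tests at 5% each, true difference zero:

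n per group = 2 × 0.29 × 0.71 × (z₀.₉₅ + z₀.₉₀)² / 0.10² = 352.66, rounded up to 353, so 706 in total.

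706 × 1.05 = 741.3, the stated 741. The base of 706 is therefore sound for what follows.

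**Step 2: number scanned at 6 months** = day-3 rate × 706.

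- At 29%: 0.29 × 706 = 204.7, about 205 scanned and 501 (71%) not scanned.
- At 45%: 0.45 × 706 = 317.7, about 318 scanned and 388 (55%) not scanned.

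**Step 3: the 6-month rate under each denominator, day-3 rate 29%.** With persistence f, the rate among those scanned is f. Over all 706, with unscanned patients counted as lesion-free, it is 0.29 × f.

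| Assumed persistence f | Among those scanned | Over all 706, unscanned taken as lesion-free |
|---|---|---|
| 25% | 25% | 7.3% |
| 50% | 50% | 14.5% |
| 75% | 75% | 21.8% |
| 100% | 100% | 29.0% |

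**Step 4: what the all-patient figure hides.** Suppose, again as an assumption, that 5% of unscanned patients had a new late lesion. The true cohort rate would be 0.29 × f + 0.71 × 0.05. That is 10.8% at f = 25% and 32.6% at f = 100%, which is 3.55 percentage points above the table's last column in every row. No data under this schedule would show the difference.

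**Step 5: direction of the trend.** With one denominator kept throughout, both versions can only stay level or fall from day 3 to 6 months: from 100% among those scanned, and from 29% over all patients. A rise, such as 29% at day 3 to 50% at 6 months, appears only if 706 is the denominator at day 3 and 205 at 6 months.

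**The case against.** The strongest reply is that nothing confirmatory is touched. The primary endpoint is the difference in MR events between the endoaortic and transthoracic clamps. That comparison, and the sample size behind it, can rest on the day-3 scan, which every patient without a contraindication receives. The only endpoint tied to the follow-up scan is the evolution of new lesions, which can be studied only in patients who have them, so the schedule suits that endpoint. All of this stands, and it limits the weight of the point.

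A second reply is that denominators and the handling of unscanned patients are usually left to an analysis plan or the full protocol. That is true in general but does not rescue this sentence. The article states an analysis for which the schedule does not collect the data, and no later detail can supply scans that were not done.

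A reader might also infer three stronger things that the article does not support:

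- **That the clamps will be compared at 6 months in a subgroup defined by the outcome.** Such a comparison would lose the protection of randomisation, but the article announces none.
- **That the planned series must show a spurious rise.** This needs denominators to be switched between time points, and the article specifies no switch.
- **That the label time series invalidates a result.** Three scans per patient are repeated binary measures, so the term is a poor fit, but the term alone changes no estimate.

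Finally, the wording after 6 months in the Abstract and in Study design and objectives could mark the start of a 6–12 month window. Statistical considerations, however, fixes the point at 6 months after surgery. Figures 1 and 2 are not available to settle it.

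**Conclusion.** The point holds as a conflict within the article: the three-point cohort rate, and any trend drawn from it, is not estimable under the stated scan schedule. At the plan's 29% rate about 71% of patients have no 6-month scan, and at 45% about 55% have none, in both cases because of their postoperative result. The figure reported at 6 months could be anything from 7.3% to 100%, depending on the denominator and on a persistence that is assumed here.

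The count of about 205 in 706 rests only on the plan's own inputs. The rates at 6 months rest on the assumed 25% to 100% persistence and, for the all-patient version, on counting every unscanned patient as lesion-free.

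The consequence is limited to a secondary, descriptive analysis. The primary comparison and the sample size are not affected if they rest on day 3. The text should be corrected, but the point ranks below those that must be fixed for the trial's main result to stand.

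**What to change.** Replace the three-point time-series sentence in Statistical considerations with two statements:

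1. The incidence of new lesions at day 3, judged against each patient's own baseline scan, among patients with both scans. The baseline scan then serves as reference and not as a first event rate.
2. Among day-3-positive patients only, the proportion whose lesions are resolved, reduced or persistent at the follow-up scan, with exact confidence intervals. State the denominator, and label the analysis descriptive and not a randomised comparison.

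Reconcile the follow-up time, which is 6 months in the Abstract, in the scan schedule and in Statistical considerations, but 6–12 months in the secondary endpoint. One time point with a stated window should appear throughout.

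The cost is wording only, with no extra scans and no change to the sample size. The downside is that no cohort-wide 6-month rate is reported, but the present schedule could not supply one. If the investigators do want that rate, it would need 6-month scans in all patients or in a random sample of those negative at day 3. That is a larger change, which the listed endpoints do not require.

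### The trial is sized to show equivalence within 10 points, but the primary endpoint is worded as a difference and none of the named analyses uses the margin

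*Protocol article*

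**What the plan says.** Four statements in the protocol article bear on this point.

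- **Abstract, Discussion:** the authors write that "we expect to show equivalence in terms of neurological events of this technique compared with the transthoracic clamp".
- **Study design and objectives:** "The primary endpoint is to assess the difference in terms of MR imaging events between the EAC and the TTC".
- **Statistical considerations, sample size:** 353 patients per group (706 in total) "would have an 80% chance of demonstrating equivalence between the EAC and theTTC, with a margin of 10% and a 95% confidence". The event rate is 29%, the bottom of a cited range of 29% to 45%. After a 5% allowance for loss to MR imaging, the total is 741.
- **Statistical considerations, analysis:** P "values will be obtained by the two-sided exact method, at the conventional 5% significance level". The next paragraph begins "The association between the occurrence of neurological events and the categorical variables will be analyzed by" and names Fisher's exact test, then Mann-Whitney for continuous variables and logistic regression for odds ratios.

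The 10% margin appears in the sample-size sentence only. No analysis sentence mentions it, a confidence interval for the risk difference, or a pair of one-sided tests.

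**The concern.** An equivalence claim needs a rule that rejects differences as large as the margin. A test of no difference cannot supply it, because a large P value may mean that the arms are alike or only that the data are too few or too variable to separate them. Here the sizing assumes an equivalence rule, the endpoint asks about a difference, and the listed tests address association.

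The error that matters is calling the two clamps equivalent when they differ by 10 points. The article's Discussion cites a meta-analysis whose subgroup result linked excess stroke risk to studies using the EAC, so false reassurance would be costly. Without a stated rule, nothing in the analysis text limits that error to 5%, and the quoted power cannot be tied to any analysis that the article names.

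**Working it through.** **Inputs.** From Statistical considerations: event rate p = 0.29, margin d = 0.10, power 80%, 353 per arm. From Randomization: equal allocation. Assumed here because the article does not say: the true difference is zero and the margin is absolute.

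**Step 1: reproduce the stated size.** For two one-sided tests with a true difference of zero:

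n per arm = 2p(1-p)(z[1-α] + z[1-β/2])² / d²

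With α = 0.05 per side and β = 0.20: 2 × 0.29 × 0.71 × (1.645 + 1.282)² / 0.10² = 352.66 (unrounded z values), so 353 per arm and 706 in total. This matches exactly.

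Alternatives:

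- α = 0.025 per side (a 95% interval): 432.70, so 433 per arm and 866 in total. No match.
- Non-inferiority: 324 per arm (α = 0.025) or 255 (α = 0.05). No match.
- A relative margin of 10% (2.9 points): about 4,194 per arm. No match.
- A two-sided difference test of 29% against 39%: 352 per arm. This is close but not equal, and the text says equivalence.

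So 353 is an equivalence size, for an absolute 10-point margin and two one-sided 5% tests. That corresponds to a 90% interval.

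**Step 2: power under each interval at 353 per arm.** The standard error is √(2 × 0.29 × 0.71 / 353) = 0.03416, and d / SE = 2.928. Power is 2Φ(d/SE - z) - 1.

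- 90% interval: 2Φ(2.928 - 1.645) - 1 = 80.0%.
- 95% interval: 2Φ(2.928 - 1.960) - 1 = 66.7%.

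**Step 3: compare the two readings of a result.** Every possible pair of event counts (354 × 354) was weighted by its binomial probability, with 353 per arm. The interval rule uses the Wald interval.

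| True rates | Fisher not significant (two-sided 5%) | 90% interval within ±10 points |
|---|---|---|
| 29% v 29% | 95.9% | 80.2% |
| 37% v 29% | 41.1% | 13.9% |
| 39% v 29% | 21.9% | 4.9% |

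At a true difference equal to the margin, non-significance occurs 21.9 / 4.9 = 4.5 times as often as the interval rule is met. With equal rates, 95.9 - 80.2 = 15.7% of trials are non-significant without showing equivalence. No outcome at equal rates was both significant and inside the margin.

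**Step 4: an example.** Take 125/353 (35.4%) against 102/353 (28.9%). The difference is 6.5 points and Fisher's P = 0.076. The standard error is √(0.354 × 0.646/353 + 0.289 × 0.711/353) = 0.0351, so the 90% interval is 6.5 ± 1.645 × 3.51, or 0.7 to 12.3 points. The test is not significant, yet the interval passes the margin.

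**Step 5: sensitivity to size.** With 50 per arm and true rates of 39% and 29%, Fisher is non-significant in 86.7% of trials. Read as equivalence, non-significance would favour the smaller trial.

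**The case against.** The strongest case on the other side has five parts.

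- **The P-value sentence is general.** It follows a sentence on event rates at three scans, and the Fisher, Mann-Whitney and logistic paragraph speaks of variables and covariates, which may be risk-factor work. No analysis sentence names clamp type. This stands: a reader might infer that Fisher's test is the primary comparison between arms, but the article does not say so. On this reading, too, the margin is used in no named analysis.
- **Nothing says that P > 0.05 will be read as equivalence.** This stands as well. The 21.9% is conditional on that reading and does not describe what the trial will do.
- **The sizing sentence already gives a margin and a confidence level.** These are the ingredients of an interval rule, and an analysis plan that is not shown may use them. So the claim that the trial has no basis at all for judging equivalence goes too far. But the article does name its tests, sidedness and level, and these do not fit the design it states. The ingredients are also ambiguous: taken literally, 95% confidence does not give 353.
- **Equivalence is not the formal aim.** It is an expectation and the basis of the sizing, while the primary endpoint concerns a difference, which Fisher's test would suit. This is correct, and it is part of the point: the sections have to be reconciled.
- **The outcome may seem to change from MR imaging events to neurological events.** The terms overlap, since the article estimates the rate of neurological events by MR scan. The text does not support a charge of outcome switching.

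**Conclusion.** The point holds as a mismatch between the stated design and the stated analysis. The sizing reproduces exactly as an equivalence design, the endpoint is worded as a difference, and every named analysis tests no association without using the margin. The 80% power is attached to a rule that the analysis text lacks.

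The size of the problem depends on what fills the gap. If non-significance were taken as equivalence, the false-equivalence rate at 39% against 29% would be about 21.9% instead of 4.9%. If a literal 95% interval were used, that error would be controlled, but power would be about 67% instead of 80%. These figures assume 353 evaluable patients per arm and an absolute margin. The power figures also assume a true rate of 29% in both arms.

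A reader might go further and infer that the investigators plan to claim equivalence from P > 0.05, or that no equivalence criterion exists anywhere. The article supports neither.

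**What to change.** Before the arms are compared, add one paragraph to the protocol or analysis plan that does the following.

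1. Reconciles the primary endpoint in Study design and objectives with the equivalence stated in the abstract and the sample-size text.
2. Names the primary analysis: the EAC minus TTC difference in the proportion of patients with MR imaging events on the third-postoperative-day scan.
3. States the rule: equivalence is concluded only if the confidence interval lies wholly within -10 to +10 absolute percentage points.
4. Fixes the level. A 90% interval (two one-sided 5% tests) keeps 706 evaluable patients and 80% power. With a 95% interval, the power must be restated as about 67% at 353 per arm, or the size raised to 433 per arm (866 in total, before the allowance for loss).
5. Keeps Fisher, Mann-Whitney and logistic P values for secondary and risk-factor analyses, and says that P > 0.05 is not evidence of equivalence.

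With the 90% interval the cost is the paragraph alone, with no new patients or data. With the 95% interval the cost is either the lower power or 866 - 706 = 160 more evaluable patients.

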### Randomization

Patients enrolled in the study are allocated to one of the two parallel treatment groups by equal randomization (Fig. 1). Randomization is conducted using an online computerized service (Sealed Envelope, London, UK). Randomization is handled by an independent statistician who is not involved in trial data collection and analysis. The surgeon is informed about the type of aortic clamping used on the day of the operation; this is facilitated using opaque envelopes containing the patient’s group which the primary investigator has received from the statistician. The primary investigator places this envelope inside the patient’s medical records just before the patient is taken to the operating room, and the surgeon opens the envelope in the operating room.

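### Optional efficiency gain: none of the listed analyses gives a baseline-adjusted risk difference to set against the 10-point margin, although the needed baseline data are already planned

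*Protocol article*

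**What the plan says.** All references are to the Protocol article, Methods/design.

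- **Sample size (Statistical considerations).** The MR event rate after sternotomy "has been reported to range from 29% to 45" per cent, and the lower value is used. On that basis "a total of 706 patients (353 patients per group) would have an 80% chance of demonstrating equivalence", "with a margin of 10% and a 95% confidence".
- **Analyses (Statistical considerations).** The association between the "occurrence of neurological events and the categorical variables will be analyzed by the Fisher’s exact test", and continuous variables are handled by the Mann-Whitney test. "The odds ratio of the occurrence of neurological events" is then to be studied in a series of univariate and multivariate binary logistic models using the same categorical and continuous covariates. P values are "obtained by the two-sided exact method, at the conventional 5% significance level".
- **Baseline data (Study design and objectives).** Before surgery "an initial MR imaging study is performed as a baseline assessment". Age is an eligibility criterion in Table 1, so it is known for everyone. In the statistical section the baseline scan appears only as the first of three time points at which the event rate is described.
- **Allocation (Randomization).** Patients are "allocated to one of the two parallel treatment groups by equal randomization". No stratification factor is named.

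**The concern.** The margin is an absolute difference in risk, so the equivalence claim rests on an interval for EAC minus TTC in percentage points. Fisher's test gives a P value, Mann-Whitney does not apply to a binary outcome by arm, and the logistic models give odds ratios. None of these is on the scale of the margin. Adding covariates to a logistic model and reading off the treatment odds ratio does not supply the missing quantity either.

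Equivalence is shown only when the whole interval lies within ±10 points, so a narrower interval raises power directly. Age and baseline lesion load are plausible predictors of new lesions and will be available before surgery. Leaving them out of the risk-difference estimate gives up some precision that could be had without new data. At stake is a modest amount of power, not the validity of the comparison.

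**Working it through.** **Inputs from the document:** event rate p = 0.29 in both arms (the true difference of 0 is implied, not stated), margin 0.10, 353 per arm, 80% power.

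**Input not in the document:** the prognostic strength of age and baseline MR lesion load. It is treated below as an assumed range.

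**1. Reproduce the plan's figure.** Two one-sided tests on a risk difference, with unpooled variance:

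n per arm = 2p(1−p)(z₁₋α + z₁₋β/₂)² / margin²

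- With 5% per side (90% interval): 2 × 0.29 × 0.71 × (1.645 + 1.282)² / 0.10² = 352.7, so 353 per arm and 706 in total. This matches the stated figure exactly.
- With 2.5% per side (95% interval): 2 × 0.29 × 0.71 × (1.960 + 1.282)² / 0.10² = 432.7, so 433 per arm and 866 in total.

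The stated size is therefore an unadjusted risk-difference calculation with a 90% interval.

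**2. Unadjusted power at 353 per arm.**

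SE = √(2 × 0.29 × 0.71 / 353) = 0.03416, and 0.10 / SE = 2.928.

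Power = 2Φ(0.10/SE − z₁₋α) − 1

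- 90% interval: 2Φ(2.928 − 1.645) − 1 = 80.0%.
- 95% interval: 2Φ(2.928 − 1.960) − 1 = 66.7%.

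**3. Gain from a standardised, adjusted risk difference.** To a good approximation the variance is multiplied by (1 − R²), where R² is the share of outcome variance explained by the baseline score. For a standard normal score with a given odds ratio per SD and an average risk of 29%, R² = Var(predicted risk) / (0.29 × 0.71). Entering SE × √(1 − R²) in the power formula gives:

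| Assumed OR per SD | R² | Power, 90% interval | Power, 95% interval |
|---|---|---|---|
| none | 0% | 80.0% | 66.7% |
| 1.3 | 1.4% | 80.8% | 67.7% |
| 1.5 | 3.2% | 81.7% | 69.0% |
| 2.0 | 8.6% | 84.3% | 72.9% |
| 2.5 | 13.6% | 86.8% | 76.6% |

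Simulation of 2,000 trials per scenario agrees closely. For odds ratios of 1.3, 1.5, 2.0 and 2.5, the adjusted variance was 0.986, 0.959, 0.927 and 0.858 of the unadjusted variance. Power with a 90% interval was 80.6%, 82.0%, 84.4% and 85.7%.

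**4. Do the planned multivariate models already deliver this?** Two further scenarios were simulated, with 4,000 runs each at 353 per arm.

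| Assumed OR per SD of age; OR for a baseline lesion | Variance of standardised risk difference, relative to unadjusted | SE of treatment log odds ratio, unadjusted to adjusted |
|---|---|---|
| 1.5; 2 | 0.93 | 0.166 to 0.172 |
| 2; 3 | 0.83 | 0.166 to 0.182 |

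The adjusted odds ratio is not estimated with a smaller SE. The precision gain appears when the same model is standardised to a risk difference.

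**5. Can adjustment rescue a 95% interval?** Restoring 80% power would need R² = 1 − 352.7/432.7 = 18.5%. That is above the 13.6% at the top of the range in step 3.

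**The case against.** The case against is substantial, and most of it stands.

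- **No primary analysis is fixed.** A reader might infer that the plan commits the primary comparison to an unadjusted Fisher's test. The document does not say so. The sentence covers categorical variables in general. If arm counts among them, it also enters the multivariate models announced in the same paragraph. Age and baseline MR are neither named nor excluded as covariates.
- **The design does not depend on adjustment.** A reader might infer that the equivalence test lacks precision without covariates. The stated size was derived with no covariate gain and reaches 80% unadjusted on its own 90%-interval basis. With 1:1 randomisation, the unadjusted comparison is also unbiased.
- **The gain is assumed.** Nothing in the document supports an odds ratio per SD of 2.0 to 2.5. Table 1 excludes previous stroke or TIA, neurocognitive impairment, peripheral vascular disease, atrial fibrillation, cerebral inflammatory disease and age over 80. These exclusions plausibly narrow the spread of baseline risk.
- **Covariate choice is commonly left to the analysis plan.** That is so, and not naming age or baseline MR is no defect in a protocol article.

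The last objection does not dispose of the scale problem. The article does state its methods, and none of them as stated produces a risk difference to set against the margin. An unadjusted risk difference with its interval would fill that gap. The standardised version fills it too and also uses baseline data that every patient is due to have. It is therefore a specific improvement, and more than a request for detail.

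**Conclusion.** This is an optional efficiency gain, not an error. The unadjusted analysis is valid and has the stated 80% power with a 90% interval at a 29% event rate. A baseline-standardised risk difference would raise power at 353 per arm to about 81-87%. That range assumes a combined baseline score with an odds ratio per SD of 1.3 to 2.5 (R² about 1% to 14%), and the lower end is more plausible in this selected population. At that end the gain is one or two points.

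A reader might also infer that adjustment makes up for the stated 95% confidence. It does not. With a literal 95% interval, power is about 67% unadjusted and at most about 77% within the assumed range. The interval level and the sample size are a separate issue and need their own resolution.

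**What to change.** In the analysis plan, define the primary estimate as the EAC minus TTC risk difference. Obtain it by standardisation (g-computation) over all analysed patients, from a logistic model with arm, age and baseline MR lesion load. Give it a robust or bootstrap interval and compare that interval with ±10 points. Report the unadjusted risk difference with its interval as a sensitivity analysis. Keep the Fisher, Mann-Whitney and odds-ratio analyses as descriptions of associated factors.

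The cost is a few lines of text and R code. The covariates, their coding (including how baseline lesion load is measured) and the estimator must be fixed before unblinding. No new patients, scans or procedures are needed, and the sample size should not be reduced in anticipation of the gain.
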